### Study design

This is a Hybrid Type 1 Implementation-Effectiveness trial designed as a two-arm randomized controlled trial (RCT), with individuals randomized (using REDCap-generated random numbers) via 1:1 allocation ratio to MB-VG or usual Judy Center services followed by delayed intervention receipt (receipt after data collection at 6-month time point). We selected an RCT design given our primary study aim to examine effectiveness of the MB-VG intervention. Women randomized to the usual care arm will be offered participation in MB-VG after completing their final data collection activity at 6 months post-randomization. We recognize this may result in MB-VG being offered beyond the period where there is greatest prevalence of depression among new mothers; however, this approach was endorsed by Judy Center partners. Specifically, they felt that in its absence some women may not consent to participation knowing they may not be able to receive MB-VG.

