### Participants

Inclusion criteria for *perinatal intervention participants* include (1) 16 years of age or greater; (2) Identify as Latina; (3) Speaks Spanish/prefers to receive services in Spanish; (4) Pregnant or have a child 9 months or younger; At risk for a major depressive episode based on the following: mild to moderate depressive symptoms [5–14] on the Edinburgh Postnatal Depression Scale [52] and/or presence of risk factors for Major Depressive Episode (MDE) onset as measured by the Postpartum Depression Predictors Index-Revised (PDPI-R) [53–55]; ≥ 3 on PDPI-R when administered prenatally or ≥ 4 on the PDPI-R postnatally, or history of depression as indicated on the PDPI-R, regardless of score). Study exclusion criteria include (1) Individuals who score > 14 on the EPDS (likely meet criteria for a current major depressive episode for whom treatment would be recommended (vs. preventive intervention for depression); (2) Individuals who are not at risk for PPD—i.e., scores < 5 on the EPDS and under the aforementioned cutoffs on the PDPI-R and no personal history of depression; (3) Staff concern about cognitive limitations of a potential participant such that there is concern that they would not understand the intervention material; (4) Staff concern about a potential participant’s capacity to engage in a group intervention (e.g., concern about disruptive behavior); and (5) Unable to speak and understand Spanish.

As part of exploratory analyses, we will recruit *children of perinatal study participants* who are between the ages of 2.5 and 4.5 years at baseline. Inclusion criteria for intervention facilitators/staff and Judy Center directors include that the staff is a facilitator or co-facilitator of MB-VG groups or a director at a site participating in the study (either referring participants or delivering via their site). We plan to enroll a total of 486 study participants: (1) 300 perinatal individuals, (2) 150 children of perinatal individuals, (3) 24 MB-VG facilitators, and (4) 12 Judy Center directors.

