**Secondary Outcomes and Intervention Mechanisms**				
Behavioral activation	Behavioral Activation Depression Scale (BADS) [67, 68]	X^**1**^		
Decentering	Experiences Questionnaire [69]	X^**1**^		
Social support	Multidimensional Scale of Perceived Social Support (MSPSS) [70]	X^**1**^		
Mood management	Patient-Reported Outcomes Measurement Information System (PROMIS) Self-Efficacy Managing Emotions [71]	X^**1**^		
Anxiety Symptoms	Generalized Anxiety Disorder 7-item (GAD-7) [72]	X^**1**^		
Perceived Stress	Perceived Stress Scale—10-item (PSS-10) [73, 74]	X^**1**^		
Food Insecurity	Household Food Security Scale-Short Form [75]	X^**1**^		
Mental Health Treatment Stigma	Stigma Concerns about Mental Health Care [76]	X^1^		

^1^ Data collected at baseline, 1-wk. Post-intervention., 3 mos. Post-intervention., 6 mos. Post-intervention; ^2^ Data collected at 6 mos. Post-intervention; ^3^ Data collected at 3- and 6-mos. Post-intervention

**Table 3 Tab3:** Overview of measures and methods to assess implementation outcomes

Implementation outcome indicator (Aim 2)	Measure(s)/metrics	Survey timing (respondents)	Sample explanatory/interview questions (Aim 3)	Interview timing (respondents)
**Reach**	% meeting eligibility criteria who enroll	Administrative/Ongoing	What explains barriers to enrollment?	Post-cohort implementation (facilitators) Post-completion of all intervention cohorts at early learning center (directors)
**Effectiveness**	See Table 2		What explains variability in effectiveness?	Post-completion of all intervention cohorts at early learning center (facilitators and directors)
**Adoption**	% sites & facilitators who begin MB-VG	Administrative/Ongoing	Barriers to center & facilitator adoption of MB-VG?	Post-completion of all intervention cohorts at early learning center (directors)

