### Quantitative analysis

Descriptive statistics will summarize baseline characteristics overall and by study arm (i.e., usual family support services vs. MB-VG). As appropriate, mean ± standard deviation (or median [inner quartile range]) will be used in cases of skewed or non-normal empirical distributions and frequency (proportions) will summarize continuous and categorical data, respectively. Analyses will employ normal theory methodology as appropriate, and in cases of violations of assumptions, transformations, and/or nonparametric analyses may be utilized. Analyses will proceed at the participant level, and all hypothesis tests will assume a two-sided 5% level of significance. We will apply the Benjamini–Hochberg correction to control family-wise type I error rate to 5%. We plan to perform all analyses using both the intent-to-treat (ITT) approach and a dose–response approach, adjusted for propensity scores. Multilevel analysis, i.e., generalized mixed effects models, will estimate baseline and multivariate adjusted between-group differences, adjusted odds ratios (AORs), and 95% confidence intervals (CIs) using individual-level data but considering the hierarchical and clustered structure of data, with participants clustered by group (i.e., Judy Center). We believe clustering by group will be very small and thus do not take it into account in the power analysis. Doing so would lead to a small increase in the minimal detectable effect sizes (e.g., increasing from 0.241 to 0.284). Continuous outcomes will use a model that assumes normally distributed outcomes, and appropriate transformations of the data will be made to improve normality. Binary outcomes will be assessed using a logistic regression-based multilevel model.

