*Exploratory outcomes*: We will conduct analyses related to our exploratory objective assessing child dysregulation and school readiness among children aged 2.5–4.5 years. For the Disruptive Behavior Diagnostic Observation Scale (DB-DOS), we will conduct a series of ANOVAs examining differences between intervention and control children on each DB-DOS subscale: anger modulation, behavioral regulation, and competence. For the Bracken School Readiness Composite, we will conduct an ANOVA comparing intervention and control children on their overall school readiness composite score.

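### The exploratory child outcomes are compared by ANOVA on arm alone across a two-year age window; adding the child's age at observation would gain precision at almost no cost

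*Protocol article*

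**What the plan says.** The paragraph on exploratory outcomes in the Quantitative analysis section names the method for all four child analyses. For the three DB-DOS subscales, "we will conduct a series of ANOVAs examining differences between intervention and control children on each DB-DOS subscale". For the Bracken composite, "we will conduct an ANOVA comparing intervention and control children on their overall school readiness composite score". Neither sentence names a covariate or a random effect.

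The Participants section recruits children "between the ages of 2.5 and 4.5 years at baseline". The footnote to Table 2 that applies to both child measures reads "Data collected at 6 mos. Post-intervention", so there is one observation per child and no baseline child score.

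The maternal outcomes are treated differently. Their models are multilevel, using individual data "but considering the hierarchical and clustered structure of data". The effectiveness paragraph adds pretest covariates and random intercepts for group and instructor, and later text applies mixed models to primary and secondary outcomes. The provisional covariates are first-time motherhood, education and use of mental health services. Child age is not among them.

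**The concern.** Dysregulation and school readiness are developmental outcomes, so scores may well depend on how old the child is. In an ANOVA on arm alone, any variance due to age stays in the error term. No pretest can remove it, because none is taken. The child comparison has half the families of the main trial, so it can least afford the loss. What is at stake is the size of effect that the exploratory aim can detect. A second, smaller question is whether children whose mothers shared an intervention group can be treated as independent.

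**Working it through.** **Number of children.** The Virtual observations section expects about half of the families to have an eligible child: 0.50 × 300 = 150, which reproduces the stated figure. The article gives no detectable effect for child outcomes.

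**Formula.** With 1:1 allocation, two-sided alpha 0.05 and 80% power (Statistical analysis section),

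MDES = (t₀.₉₇₅ + t₀.₈₀) × √[(1 − R²) / (0.25 N)],

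where R² is the share of outcome variance explained by covariates.

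**Check against the plan's maternal figures.** At N = 300 and R² = 0 the formula gives 0.325, not the stated 0.241. With R² of about 0.45 it gives 0.241 at N = 300 and 0.269 at N = 240, matching both stated figures. The article states no R², so 0.45 is inferred. It does show that the stated maternal figures fit a calculation that counts on covariates.

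**Plain ANOVA for the children (R² = 0).**

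- N = 150, 148 degrees of freedom: (1.976 + 0.844) × √(4/150) = 2.820 × 0.1633 = 0.46 SD.
- N = 120, 118 degrees of freedom: (1.980 + 0.845) × √(4/120) = 2.825 × 0.1826 = 0.52 SD. Here 120 = 0.80 × 150 assumes that the attrition stated for the trial also applies to children. The article itself expects 150 to provide data.

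**With child age as covariate.** The documents give no R² for age, so a range is assumed:

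| Variance explained by age | MDES, 150 children | MDES, 120 children |
|---|---|---|
| 0% (score already age-normed) | 0.46 | 0.52 |
| 10% | 0.44 | 0.49 |
| 30% | 0.39 | 0.43 |
| 50% | 0.33 | 0.36 |

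At 30% the gain equals 1/(1 − 0.30) = 1.43 times the number of children.

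**Chance age imbalance.** If age is uniform over two years, its SD is 2/√12 = 0.577 years. With 75 children per arm, the difference in mean age has standard error 0.577 × √(2/75) = 0.094 years, or about 1.1 months. The ordinary standard error of the ANOVA already covers this variation.

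**Clustering.** Only the intervention arm has groups. With m children per group and intraclass correlation ICC, the variance of the arm difference is inflated by V = [1 + (m − 1)ICC + 1]/2, and the true alpha is 2[1 − Φ(1.96/√V)]. Both m and ICC are assumed:

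- m = 2.5, ICC = 0.02: V = 1.015, alpha 5.2%.
- m = 5, ICC = 0.10: V = 1.20, alpha 7.4%.

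**The case against.** **The article is a condensed text.** It never calls the ANOVAs unadjusted, and it leaves covariates to a statistical analysis plan. This has some weight. But that deferral stands under the effectiveness models, and the mixed models are assigned to primary and secondary outcomes. For the child outcomes the article does not stay silent: it names a different method, with arm as the only factor.

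**Omitting age is not an error of validity.** This stands in full. Under randomization with equal visit timing the comparison is unbiased. What remains is lost precision on outcomes labelled exploratory.

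**The size of the gain is not documented.** This also stands. The R² values are assumptions, and the article does not say whether the Bracken composite is raw or age-standardized. For an age-standardized score the gain may be close to nothing.

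**Three stronger readings are tempting, and the documents do not support them.**

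- *The arms differ in age at observation.* The Study design section has usual-care women offered the intervention "after completing their final data collection activity at 6 months post-randomization". Taken literally, against a visit six months after the intervention in the other arm, intervention children would be older by between 9 weeks (2.1 months) and 1 month plus 15 weeks (4.5 months). But Table 2 and the Virtual observations section set one schedule, 6 months post-intervention, without distinguishing the arms. The wording needs reconciling; it does not establish that the visits differ.
- *Ignoring clustering makes the standard errors seriously too small.* Usual-care mothers attend no intervention group until their data collection has ended, so about half the children have no group. Clustering by Judy Center does not shrink the standard error of the arm comparison either, because women are randomized individually and nothing confines a center to one arm. The inflation implied by the plan's own figures, (0.284/0.241)² = 1.39, would give a true alpha of 9.6%, but only if a figure for the whole maternal sample applied in full to this half-clustered subset.
- *The maternal model should simply be reused.* First-time motherhood is defined as having no children at baseline. Every mother in this subset has an older child, so that covariate is constant. Usual-care mothers also have no intervention group or instructor.

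**Conclusion.** The point holds as a modest, optional improvement. The article fixes an arm-only ANOVA for outcomes that may depend on age, in children recruited across exactly two years of age, with no baseline child measure. The cost is precision: a minimal detectable effect of 0.46 SD with 150 children, or 0.52 SD with 120. It could be as low as 0.33 or 0.36 SD if age explained half the variance, and would be unchanged if age explained none. The size rests on the assumed R² range and, for 120, on assumed child attrition. That the comparison is unbiased rests on equal visit timing. Clustering is secondary, with a true alpha of about 5.2% to 7.4% under the assumed group sizes and correlations.

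**What to change.** Replace each ANOVA by a linear model (ANCOVA) with arm and the child's exact age at observation. This matters chiefly for the DB-DOS subscales, and for the Bracken composite if it is not age-standardized; the plan should state which score is used. Do not carry over the full maternal model, and omit the first-time-mother covariate. If clustering is to be covered, use a random intercept for intervention group in that arm only, or cluster-robust standard errors with each usual-care child as its own cluster. Reconcile the Study design wording on the final usual-care visit with Table 2.

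The age term costs one degree of freedom (148 to 147 with 150 children). No new data should be needed: the article does not say outright that age is recorded, but eligibility cannot be applied without it. The change is to wording, and should be made before the child outcomes are analysed.

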### Qualitative analysis plan and mixed methods integration

Audio files will be transcribed (and translated, when applicable). Data will be organized with NVivo Version 12 and analysis guided by the process of constant comparison [88]. Transcript coding will be primarily deductive based on implementation domains (Reach, Adoption, Implementation, Maintenance) and constructs from the Consolidated Framework for Implementation Research constructs [89] but we will use inductive coding when these codes do not appear to adequately explain the aspect of implementation described. Two team members will independently code each transcript with regular meetings used to discuss updates to the codebook and gain consensus on any disagreements in coding. Themes will be developed by reviewing excerpts associated with codes, visually mapping relations between codes, identifying broader domains suggested by codes and discussing how codes do or do not relate to constructs of interest. We will merge quantitative and qualitative data using joint displays demonstrating key quantitative and qualitative findings [89] and linking contextual factors to understand variability in effectiveness and implementation outcomes. Joint displays facilitate assessment of convergence or divergence in data within constructs and can elucidate necessary next steps to build upon study results [50].

### Safety considerations and procedures

Any participant whose responses on the EPDS (or subsequent assessments) indicate that they have had thoughts about their death or suicide within the past month will be asked additional questions to determine the suicidality degree, including whether they have experienced thoughts of their own death, thoughts about suicide, a specific plan or details about how they might take action, and any attempts they have made to hurt themselves. If assessments have been self-administered (e.g., EPDS), participants will via REDCap automatically receive information about 24/7 Spanish-language resources (e.g., National Suicide Prevention Hotline, Postpartum Support International, and the National Maternal Mental Health Hotline). Participants will be required to acknowledge receipt of these resources. In addition, designated study personnel will be immediately alerted by email and text via the survey notification function in REDCap and will reach out to and assess participants within 24 h. In this assessment, participants will be asked additional questions to determine the suicidality degree, including whether they have experienced thoughts of their own death, thoughts about suicide, a specific plan, or details about how they might take action, and any attempts they have made to hurt themselves. Study staff will also reach out to the referring Judy Center to work collaboratively to coordinate referrals for additional services if needed (case management is a core component of the Judy Center). In addition to events prompting safety protocol as above (reporting suicidal ideation on assessments), individuals who have a clinically significant finding of a CES-D score > 40 at any time point will trigger the use of our safety protocol (including text alert to PI via REDCap if completed independently) to ascertain whether there is any risk for self-harm. We will do analysis quarterly to assess for any iatrogenic effects. Text messages in MB-VG are designed to be unidirectional and primarily focused on reminding participants to practice skills and provide reminders about sessions and resources. However, it is possible that participants may respond to messages. Participants will be notified that the system is automated and that it does not constitute direct communication with a provider or therapist. Additionally, the platform will be programmed such that and research staff will be notified via text message and/or email if a keyword is texted via the SMS platform that express potential for self-harm, such as “die,” “suicide,” and “kill”. Additionally, if the participant types one of these keywords, a text message will be automatically sent to the participant like those described above. Prior to initiating the study/intervention, the research team will work with each Judy Center to confirm their client risk assessment procedures, which typically include immediate notification of relevant center staff (e.g., case manager or center director/supervisor), risk assessment, provision of local resources, or emergency referral.

*Criteria for discontinuation from intervention*: Participants will be discontinued from the intervention if they (1) develop a severe medical (e.g., bedrest due to pregnancy complications) or mental health condition (e.g., psychosis, active mania) preventing the participant from engaging in the intervention and/or understanding the intervention; (2) indicate a preference not to continue in the intervention; or (3) experience pregnancy loss or neonatal/infant loss. In the case of a participant experiencing a pregnancy or infant loss, the study team will discuss intervention continuation with the participant. We anticipate most participants will prefer not to continue in the intervention given its focus on mothers and babies. When a subject discontinues from MB-VG but not from the study, remaining study procedures will be completed as indicated by the study protocol. The exception will be the removal of all parenting-related assessments for participants who experienced a pregnancy or infant loss.

*Adverse event monitoring*: For this trial, there are three potential adverse events that will be monitored and logged: (1) movement into the severe depressive symptom range, (2) suicidal ideation, and (3) potential child abuse/neglect. There is nothing about the MB-VG intervention (including prior related MB studies) that suggest that they will generate any of these adverse events, but each will be monitored nonetheless. All adverse events occurring while on study will be documented in REDCap appropriately regardless of relationship. We will follow Institutional Review Board Adverse Event Reporting guidelines and will also report adverse events to the study Data and Safety Monitoring Board.

## Discussion

To our knowledge, this study will be one of the first to test the efficacy of a group-based virtual *perinatal depression* intervention to Latina immigrants, for whom stark *disparities* exist in access to *mental health services* [10]. Use of a virtual format for mental health interventions, including group interventions, expanded rapidly during the COVID-19 pandemic [40, 90]. In the virtual format will facilitate the incorporation of supplementary content (e.g., group discussions with a pediatrician, inclusion of a resource advocate) that may be of particular benefit to immigrant Latinas. Our hybrid effectiveness-implementation design will allow rigorous examination of barriers and facilitators to delivery of the intervention package (including supplemental components) which will provide valuable information on factors influencing intervention effectiveness and the scalability of intervention components. Similarly, implementation of the intervention in early childhood programs provides a unique setting in which to reach individuals who might not otherwise access mental health services. Addressing maternal depression has been identified as a critically needed enhancement to early childhood programs [91] yet most previous RCTs have focused on home-based programs. [92].

There are several potential challenges and practical issues to consider. First, we expect there will be some degree staff turnover at Judy Centers, turnover is an important and prevalent challenge to scaling and sustaining evidence-based mental health interventions [93]. Given this, we plan to explicitly assess center director perceived barriers to sustainment of the intervention. Challenges recruiting perinatal participants may occur which could lead to lag time between study enrollment and intervention delivery. To minimize attrition and decrease wait time between enrollment and intervention start, we will allow for smaller (e.g., 4–5 participants) intervention cohorts and for cohorts combining individuals from across Judy Centers. The virtual format facilitates combining individuals from across Judy Centers; with the impact of blended versus single-center cohorts on effectiveness and implementation explored through our qualitative data collection activities. Additionally, as multiple Judy Center staff will be trained on MB-VG, it is possible they will use intervention language and activities during their work with participants randomized to the usual care arm. Study investigators have successfully addressed this in previous trials by clearly communicating study protocols to all agency staff. Moreover, our delayed intervention design means that control participants will be able to receive MB-VG thus minimizing concern among staff that participants will not benefit from intervention content.

